## Abstract

**Background:**

Postoperative delirium is considered a serious complication in older patients. Older patients often suffer from several concomitant diseases. The reduced physical condition can increase the risk of cardiac, pulmonary and neurocognitive complications during and after surgery. SARS-CoV-2 infection primarily affects the respiratory tract but can also damage other organ systems such as the heart and brain. Given the wide range of pulmonary, cardiac and neurocognitive complications caused by SARS-CoV-2, these risks must be given special consideration during planned surgical procedures. Both surgical procedures and anesthesia are risk factors for postoperative complications in themselves. The specific impact of prior SARS-CoV-2 infection on perioperative complications in older patients has not been sufficiently researched. The aim of this study is to understand how a previous SARS-CoV-2 infection influences the occurrence of perioperative complications.

**Methods:**

In this case-control study, the data of patients over 60 years of age undergoing elective surgery are analyzed. Subjects are divided into two groups based on their SARS-CoV-2 infection status: those with a documented previous infection and those without. Confirmation of infection will be based on written evidence and anamnestic information. The primary endpoint of the examination is the occurrence of delirium within the first five postoperative days. In addition, further cardiac, pulmonary and neurocognitive complications are recorded in the perioperative period. The occurrence of postoperative delirium is recorded during the daily ward round in the first five days after surgery. The 3DCAM test and the 4AT are used for this purpose. In addition, the CAM-ICU will be used in the intensive care unit. The recruitment will include 266 patients. Statistical analyses will be performed to determine the correlation between a previous SARS-CoV-2 infection and the observed clinical outcomes.

**Discussion:**

The results of this study will provide new insights into the impact of prior SARS-CoV-2 infection on perioperative complications in older patients undergoing elective surgery.

**Trial registration:**

Deutsches Register Klinischer Studien: DRKS00034861.

## Background

Investigating the effects of surgical interventions under general anesthesia on the human organism is a crucial focus of scientific research. In view of the globally aging population, there is great interest in ensuring safe and high-quality surgical care for the older patients.

Older people are often affected by multiple comorbidities. The patient’s reduced physical condition can increase the risk of cardiac, pulmonary and neurocognitive complications during and after surgery. In addition, age-related changes in the brain lead to reduced reserve capacity [1]. Among older individuals, this can increase the risk of postoperative delirium. Postoperative delirium is considered a serious complication in older patients and is also the most common after surgery and associated with prolonged need for care. The strongest predictor of postoperative delirium is pre-existing cognitive dysfunction [2]. However, the frequency of postoperative delirium in older patients with cognitive deficits can be reduced by targeted measures [3]. Consequently, it is important to identify patients with risk factors and adapt perioperative management accordingly.

The SARS-CoV-2 pandemic has brought additional challenges in hospital and perioperative management [4]. COVID-19 is generally known to affect the respiratory tract. A SARS-CoV-2-infection can also have effects on other organ systems such as the heart, brain, liver and kidneys [5].

Within months of a COVID-19 disease, functional limitations of the lungs could be detected. This was demonstrated by examinations of lung function, physical fitness, oxygen supply during physical exertion and radiological findings. For this reason, systematic follow-up care is recommended, especially after severe courses of COVID-19 [6].

The effects of SARS-CoV-2 on the lungs can be devastating, depending on the course of the disease, age and comorbidities. The impairment of lung function also increases the likelihood of cardiac and vascular complications. An international initiative proposed that surgery should be delayed for at least 7 weeks following a SARS-CoV-2 infection [7]. However, there remains limited knowledge regarding the long-term effects of Covid-19 disease on perioperative complications and morbidity.

As the virus can also damage the brain, neurological complications have gained significant attention. The endothelial cells of the brain express ACE2 receptors and are therefore susceptible to infection with SARS-CoV-2 [5,8]. Known long-term neurological symptoms include smell and taste disorders, headaches, muscle pain, memory problems, anxiety and sleep disorders. SARS-CoV-2 can also cause states of confusion (delirium) and agitation [9]. Older patients with pre-existing cognitive impairment are particularly at risk.

Given the multiple pulmonary, cardiac and neurocognitive complications caused by SARS-CoV-2, these must also be considered in upcoming surgical procedures. This is because both the surgical procedure and the anesthesia itself already represent risk factors for possible postoperative complications.

Currently, there is great uncertainty about the long-term consequences of SARS-CoV-2 infection in the perioperative setting. There is limited valid and generalizable data on the occurrence of perioperative complications in patients with previous SARS-CoV-2 infection, particularly in the older population. New studies are therefore needed to determine the long-term effects of SARS-CoV-2 infection on perioperative cardiac, pulmonary and neurocognitive complications in older patients.

## Methods and design

### Ethics statement

This study has been approved by the Ethics Committee of the Ludwig-Maximilians-Universität München (LMU Munich). The ethics committee reviewed and approved the study protocol under the reference number 23-0552. Informed written consent was obtained from all participants involved in the study. The study has been conducted in accordance with the Declaration of Helsinki and all applicable ethical regulations.

### Outcomes

The aim of the study is to investigate effects of a previous SARS-CoV-2 infection on the perioperative care and outcome of older patients with a focus on the incidence of postoperative delirium.

#### Primary outcome measures.

The primary aim is to determine the incidence of postoperative delirium on one of the first five days after surgery in the case group compared to the control group. The endpoint will be considered met if postoperative delirium is detected with at least one of the applied assessment methods used.

#### Secondary outcome measures.

Intraoperative ventilation settings will be evaluated. Additionally, the incidence of unplanned postoperative ventilation, oxygen therapy, ARDS, respiratory insufficiency, pneumonia, pulmonary embolism, pneumothorax, myocardial infarction, myocardial damage, cardiac death, cardiac arrhythmias, atrial fibrillation, stroke, acute renal failure and other serious postoperative complications are going to be analyzed.

### Number of participants

A priori test strength analysis was performed to estimate the required number of participants. This results in a total study population of 242 participants with a required sample size of 121 participants per group. To ensure the calculated minimum level of power with the possibility of dropouts this number is increased by 10%. This results in a final planned sample size of 266 participants. Recruitment started on 06.09.2023 with the approval of the ethics vote and is expected to end on 31.12.2024.

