The study participants are then divided into two cohorts. The case group includes of patients over 60 years of age undergoing elective surgery under general anesthesia lasting more than one hour and a previous SARS-CoV-2 infection. The control group includes of patients over 60 years of age undergoing elective surgery under general anesthesia lasting more than one hour without a previously diagnosed SARS-CoV-2 infection. Both groups have an equal number of patients.

Routine laboratory parameters will be recorded as part of the preoperative surgical admission and examination. All laboratory parameters relevant to the study will be extracted and documented from the patient’s electronic file, if available. These include C-reactive protein (CRP), hemoglobin, creatinine, interleukin 6, urea, glucose, sodium and potassium.

Data on the surgical procedure is also collected, such as the urgency of the operation, the surgical specialty, the surgical technique, the duration of the operation, anesthesia technique, airway management, whether epidural anesthesia was performed, the duration of anesthesia and the extent of blood transfusions. Additionally, preoperative parameters from the anesthesia protocol will be collected, such as oxygen partial pressure, carbon dioxide partial pressure, inspiratory oxygen concentration (if oxygen was administered), pH, respiratory rate, blood pressure, heart rate, temperature and oxygen saturation. These parameters are recorded both during and after surgery. Intraoperative ventilation parameters to be included in the data collection are ventilation mode, driving pressure, plateau pressure, positive end-expiratory pulmonary pressure, compliance, tidal volume, and mean arterial pressure (MAP). All intraoperative complications including arrhythmias, hypotension, drop in oxygen saturation, blood loss and other events are documented. Anesthesia and surgery treatment data will be extracted from the hospital’s KAS data information system using surgical and anesthesia protocols. All data is recorded before, during and after anesthesia.

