Postoperative parameters	PaO_2_, PaCO_2_, FiO_2_, pH value, respiratory rate, blood pressure, heart rate, temperature, SpO_2_, hemoglobin
Postoperative care	admission to the intensive care unit, reason for admission to the intensive care unit, occurrence of nausea and vomiting, pain intensity, need for oxygen therapy or mechanical ventilation, reason for oxygen therapy and mechanical ventilation, complications during the first 5 postoperative days
Postoperative pain therapy	opioids, peripheral analgesics, regional analgesics, other
Postoperative delirium screening	on postoperative days 1–5 using 3DCAM, 4AT and CAM-ICU in the intensive care unit

The occurrence of postoperative delirium is assessed during daily rounds by trained staff in the first five days after the operation, in accordance with the European guideline. The 3DCAM test and 4AT are used for this purpose.

Additionally, the CAM-ICU (Confusion Assessment Method for the Intensive Care Unit) is routinely used by medical staff in the intensive care unit. All three instruments are validated and reliable screening methods for detecting delirium [14,15].

Withdrawal from the study happens may occur after the patient revokes consent, the planned operation is canceled, or if the study protocol is violated. All study participants are visited on all five postoperative days. To determine the incidence of delirium and other complications, such as cardiac and pulmonary, only patients who have spent at least one night on a surgical ward after surgery and who have undergone at least one postoperative screening will be included. Patients who do not complete these criteria are excluded from the statistical analysis. This methodological approach ensures a careful and representative analysis of postoperative events.

A recruitment period of approximately 16 months is planned to include 266 patients. A dropout rate of 10% of the recruited patients will be tolerated. If the dropout rate exceeds this threshold, further recruitment will be undertaken. The conduct of this study was guided by the recommendations of the STROBE checklist (Strengthening the Reporting of Observational Studies in Epidemiology) to ensure transparency and scientific rigor. All relevant points of the checklist were considered in the planning and conduct of the study to maximize the quality and reproducibility of the results.

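### The 10% increase to 266 does not quite cover the tolerated 10% dropout: 25 or 26 losses leave 241 or 240 of the required 242 patients without triggering replacement (minor)

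*Protocol article*

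**What the plan says.** The section on the number of participants in the protocol article gives the requirement: "This results in a total study population of 242 participants with a required sample size of 121 participants per group". It then adds a margin and states its purpose: "To ensure the calculated minimum level of power with the possibility of dropouts this number is increased by 10" per cent. The outcome is "This results in a final planned sample size of 266 participants".

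The Study design section sets the operating rule. It fixes the tolerated rate and its base, "A dropout rate of 10% of the recruited patients will be tolerated", and says when action follows: "If the dropout rate exceeds this threshold, further recruitment will be undertaken". The same section asks for groups of equal size ("Both groups have an equal number of patients"). It also removes from the analysis patients who did not spend at least one postoperative night on a surgical ward or had no postoperative screening: "Patients who do not complete these criteria are excluded from the statistical analysis".

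**The concern.** The margin and the tolerated loss are both called 10%, but they have different bases. The margin is 10% of the patients required (242). The loss is 10% of the patients recruited (266), which is a larger number. A margin of 10% on the smaller base cannot absorb a loss of 10% on the larger one.

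This would be a harmless convention if the 10% were only a rough allowance. Here it is also the threshold for replacement. Between the point where the margin is used up and the point where recruitment resumes, the study can fall below its own minimum while its safeguard stays inactive. At stake is the stated assurance that the calculated minimum power is kept.

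**Working it through.** **Inputs, all from the article:** required total 242 (121 per group); increase of 10%; planned total 266; tolerated dropout 10% of recruited patients; further recruitment only above 10%.

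**1. Reproducing the planned size.** Required × (1 + 0.10) = 242 × 1.10 = 266.2, reported as 266. By group, 121 × 1.10 = 133.1, so 133 × 2 = 266. The multiplication is correct as described.

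**2. Losses the margin covers.** 266 − 242 = 24, and 24/266 = 9.02%.

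**3. What the replacement rule does near the threshold.**

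| Losses of 266 | Rate | Evaluable | 242 kept? | Further recruitment? |
|---|---|---|---|---|
| 24 | 9.02% | 242 | yes | no |
| 25 | 9.40% | 241 | no | no |
| 26 | 9.77% | 240 | no | no |
| 27 | 10.15% | 239 | no | yes |

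The rule fails for two outcomes only, 25 and 26 losses.

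**4. Size that would cover 10% of recruited patients.** Required / (1 − 0.10) = 242/0.90 = 268.9, so 269. With equal groups, 121/0.90 = 134.4, so 135 per group and 270 in total. The usual rounding up leaves a little slack: with 268 recruited, 26 losses (9.70%) leave exactly 242, and a 27th (10.07%) triggers recruitment.

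**5. Effect on power.** The article reports only that "A priori test strength analysis was performed to estimate the required number of participants"; it does not give alpha, power or delirium rates. These must be assumed.

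- Assume rates of 15% and 30%, two-sided alpha 0.05, and the two-proportion normal approximation with pooled variance under the null: power = Φ{[0.15√n − 1.960√(2 × 0.225 × 0.775)] / √(0.15 × 0.85 + 0.30 × 0.70)}. For n = 121 per group this is (1.650 − 1.157)/0.581 = 0.848, power 80.2%. For n = 120 it is (1.643 − 1.157)/0.581 = 0.836, power 79.8%. The loss is about 0.3 points.
- Without assuming rates, if 242 patients give a design power of 80% or 90% at two-sided 0.05, then power at 240 = Φ[(1.960 + z) × √(240/242) − 1.960], where z = 0.842 or 1.282. This gives 79.7% or 89.8%, a loss of about 0.3 or 0.2 points.

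**The case against.** The other side has good arguments. The calculation contains no slip: the text says the number is raised by 10%, and 266 is what that gives. Multiplying by 1 + d instead of dividing by 1 − d is a common simplification, and 266 differs from 269 or 270 by only 1% to 2%. Further recruitment is already planned, without a stated cap. Two patients matter far less than the uncertainty in any assumed delirium rate. All of this stands, and it is why the point is minor. It does not remove the mismatch, because the article itself fixes the base of the dropout rate and makes 10% the action threshold.

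A reader might infer three stronger things that the article does not support.

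- *That the tolerated dropout leaves 239 patients.* 266 × 0.90 = 239.4 is not an attainable count. 239 requires 27 losses, which is 10.15% and already triggers recruitment. The lowest total reachable without a trigger is 240.
- *That the study would be underpowered.* The target power is not given, and under the assumptions above the loss is a fraction of a point. Falling below 80% has meaning only if 80% was the target.
- *That patients excluded from the analysis are not counted as dropouts, so the gap is wider.* The article does not say so. The exclusion rule stands directly before the dropout rule, so counting those patients as dropouts is at least as natural a reading, and the full protocol may define the term.

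**Conclusion.** The point holds in a narrow form. The planned size of 266 keeps the required 242 for up to 24 losses (9.0%), not for the 10% of recruited patients that the Study design section accepts. At 25 or 26 losses the study is 1 or 2 patients short in total and the replacement rule does not act. This finding needs only the article's own figures. The power effect, about 0.2 to 0.3 points, rests on an assumed two-sided alpha of 0.05 and an assumed design power or assumed delirium rates. Severity is minor: a stated assurance and a stated threshold disagree slightly, and no estimate or test is likely to change because of it.

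**What to change.** Choose one of two corrections to the figures:

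- keep 266 and restate the tolerated loss as 24 patients (9%), which costs no extra recruitment; or
- state 270 recruited patients, 135 per group, if a loss of 10% of recruited patients is to be covered, which costs 4 more patients.

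In either case, replace the overall 10% trigger with the requirement itself: recruit further when fewer than 121 evaluable patients remain in either group. An overall count protects both groups only if losses are balanced. From 133 per group, 24 losses keep 121 in each only if they fall 12 and 12. Thirteen losses in one group and none in the other leave 120 in that group at an overall rate of 13/266 = 4.9%. A trigger on evaluable patients per group follows the article's own requirement and also makes it unnecessary to settle which losses are called dropouts. The change is one figure and one sentence.

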### Inclusion criteria

patients aged 60 years or olderpatients with an elective surgical procedure lasting 1 hour or morepatients undergoing surgery under general anesthesiapatients capable of giving consentsigned declaration of consent from the patient

### Exclusion criteria

emergency surgerypatients with language barrierspatients with preoperative delirium during hospital admissionunwillingness to follow the study protocol

### Recruitment

The selection of participants for the study will take place at the anesthesia outpatient clinic of the University Hospital Munich, LMU Munich. A structured approach will be followed to identify and include all patients who fulfill the defined inclusion criteria and do not meet any of the exclusion criteria.

### Consent

Information regarding the study is provided both verbally and in writing during the preoperative anesthesia informed consent discussion. In this context, potential study participants are presented with an information sheet that explains the objectives, procedure, potential risks and benefits of the study in detail. Patients receive a copy of the information sheet for their personal use.

A detailed Covid history is also recorded. This includes the number and time of Covid infections, as well as the time between the last infection and the operation. In addition, postoperative pain, including pain therapy and postoperative nausea and vomiting are determined.

### Duration of the study

The total duration of the study is planned to be 15 months.

### Study design

This study follows a case-control design and is conducted both retrospectively and prospectively as a non-interventional observational study.

The first phase contains a retrospective analysis of an ongoing, non-interventional delirium study. The generated data will be included in the study. Additional participants are included to optimize the number of cases and to increase the statistical significance.

Patients who meet the specified inclusion criteria and do not meet any exclusion criteria are informed about the study during their anesthesiology consultation. After being provided with information and an appropriate reflection period, the participants give their written consent to participate by signing the consent formular.

All patients undergo routine frailty screening. This is performed by specially trained staff, who also perform the Mini-Cog test. In addition, all study participants undergo a Montreal Cognitive Assessment (MOCA) and the 3-dimensional Cognitive Assessment Method (3DCAM), which are a prerequisite for inclusion in the study. The MOCA test is used to further assess the patient’s cognitive state, which can affect the postoperative outcome and the incidence of postoperative delirium.

Demographic data, the Clinical Frailty Scale, the frailty criteria according to Fried, the physical status according to the American Society of Anesthesiologists (ASA), the functional status, main diagnoses, relevant previous illnesses and the patient’s current medication are recorded in an anamnesis form. The current medication is analyzed with a particular focus on specific drugs that may impact the study outcome. These include anticholinergics, antihypertensives, benzodiazepines, tricyclic antidepressants, selective serotonin reuptake inhibitors (SSRIs), hypnotics and opioids. The total number of drugs administered is also recorded in this context. This information is extracted from the NarkoPrämed system (IMESEO GmbH, Gießen, Germany).

In addition, a detailed history of smoking, chronic pain and COVID-specific medical history is obtained. Patients are interviewed about details of a SARS-CoV-2 infections and the dates of these infections. If the exact date of the last positive PCR test is unknown, participants are categorized into specific time intervals: less than 7 weeks, less than 3 months, less than 6 months, less than 1 year or more than 1 year. The COVID-related medical history also includes questions about the symptoms and their severity that occurred in the course of the COVID-19 disease. All presurgical data are summarized in Table 1.

**Table 1 pone.0323599.t001:** Presurgical data.

Presurgical data	Items
Demographic data	age, gender, height, weight, BMI
Risk classification	Clinical Frailty Scale, frailty criteria according to Fried, ASA, functional status, PONV risk
Risk factors	smoking history, alcohol consumption, chronic pain
Diseases	diagnosis, previous illnesses
Long-term medication	anticholinergics, benzodiazepines, tricyclic antidepressants, SSRIs, hypnotics, opioids, other, number of medications
COVID-specific medical history	previous SARS-CoV-2 infection, time of last SARS-CoV-2 infection, symptoms, severity of symptoms, complications, symptoms still present, long-COVID or post-COVID, SARS-CoV-2 vaccination status, time of last vaccination
Routine laboratory parameters	C-reactive protein, haemoglobin, creatinine, interleukin 6, urea, glucose, sodium, potassium
Surgical discipline	Orthopedics, Trauma surgery, Gynecology & Obstetrics, Upper GI tract, Lower GI tract, Hepato-biliary, Endocrine surgery and pancreas, Head and neck, Breast surgery, Cardiac, Thoracic (esophagus), Thoracic (lung and other), Vascular, Urology and kidney, Plastic/ dermatologic surgery, Other
Cognitive impairment	MOCA-Test, Mini Cog-Test

The four primary symptoms of COVID-19 disease are specifically recorded. These are cough, fever, runny nose and disturbance of the sense of smell and/or taste [10]. In addition, information about possible complications of the COVID disease, currently still existing symptoms, the possible presence of a long-COVID or post-COVID syndrome, vaccination status and past hospitalization are collected. Supporting S1 Fig presents the SPIRIT schedule of the study.

The study participants are then divided into two cohorts. The case group includes of patients over 60 years of age undergoing elective surgery under general anesthesia lasting more than one hour and a previous SARS-CoV-2 infection. The control group includes of patients over 60 years of age undergoing elective surgery under general anesthesia lasting more than one hour without a previously diagnosed SARS-CoV-2 infection. Both groups have an equal number of patients.

Routine laboratory parameters will be recorded as part of the preoperative surgical admission and examination. All laboratory parameters relevant to the study will be extracted and documented from the patient’s electronic file, if available. These include C-reactive protein (CRP), hemoglobin, creatinine, interleukin 6, urea, glucose, sodium and potassium.

Data on the surgical procedure is also collected, such as the urgency of the operation, the surgical specialty, the surgical technique, the duration of the operation, anesthesia technique, airway management, whether epidural anesthesia was performed, the duration of anesthesia and the extent of blood transfusions. Additionally, preoperative parameters from the anesthesia protocol will be collected, such as oxygen partial pressure, carbon dioxide partial pressure, inspiratory oxygen concentration (if oxygen was administered), pH, respiratory rate, blood pressure, heart rate, temperature and oxygen saturation. These parameters are recorded both during and after surgery. Intraoperative ventilation parameters to be included in the data collection are ventilation mode, driving pressure, plateau pressure, positive end-expiratory pulmonary pressure, compliance, tidal volume, and mean arterial pressure (MAP). All intraoperative complications including arrhythmias, hypotension, drop in oxygen saturation, blood loss and other events are documented. Anesthesia and surgery treatment data will be extracted from the hospital’s KAS data information system using surgical and anesthesia protocols. All data is recorded before, during and after anesthesia.

After surgery, any relevant clinical data and complications that occur during the first five postoperative days are documented. Primarily, delirium and potential postoperative complications, such as nausea and vomiting (PONV) and pain are recorded. The Apfel-Score is used to estimate the postoperative PONV risk. The following factors each represent one point: female gender, non-smoker, PONV history and postoperative opioid administration. The higher the score, the higher the risk of PONV [11]. Pain intensity is assessed using the Numerical Rating Scale (NRS, 0 = no pain, 10 = worst pain imaginable), and the administered pain therapy is also documented [12]. The PONV Intensity Scale according to Wengritzky quantify postoperative nausea and vomiting [13].

Further documentation includes intensive care unit (ICU) admission, patient orientation (time, place, person, situation), prolonged or newly initiated oxygen therapy and the need for mechanical ventilation postoperatively. Postsurgical complications occurring on the day of surgery are reviewed in patient files, particularly the anesthesia protocol, using the Nu-DESC (Nursing Delirium Screening Scale) and anesthesia progress observations (AVB). All treatment data are summarized in Table 2.

**Table 2 pone.0323599.t002:** Treatment data.

Treatment data	Items
Surgery	elective, emergency
Surgical technique	one-lung ventilation during the procedure, open abdominal surgery, open thoracic surgery, laparoscopic surgery, thoracoscopic surgery, laparoscopically or thoracoscopically assisted, robot-assisted surgery (e.g. daVinci surgery), other
Duration of surgery	start of surgery, end of surgery
Anesthesia	total intravenous anesthesia (TIVA), general (volatile), general (balanced)
Airway management	endotracheal tube, endobronchial blocker (tracheostomy), double-lumen endotracheal tube, laryngeal mask
Epidural anesthesia	none, thoracic, lumbar
Duration of anesthesia	start of anesthesia, end of anesthesia
Hydration balance	transfusion, blood loss
Preoperative parameters	PaO_2_, PaCO_2_, FiO_2_, etCO₂, pH value, respiratory rate, blood pressure, heart rate, temperature, SpO_2_
Intraoperative parameters	PaO_2_, PaCO_2_, FiO_2_, etCO₂, pH value, respiratory rate, blood pressure, heart rate, temperature, SpO_2_, ventilation mode, Pmax, plateau, PEEP, compliance, respiratory minute volume, VT, MAP, complications
Postoperative parameters	PaO_2_, PaCO_2_, FiO_2_, pH value, respiratory rate, blood pressure, heart rate, temperature, SpO_2_, hemoglobin
Postoperative care	admission to the intensive care unit, reason for admission to the intensive care unit, occurrence of nausea and vomiting, pain intensity, need for oxygen therapy or mechanical ventilation, reason for oxygen therapy and mechanical ventilation, complications during the first 5 postoperative days
Postoperative pain therapy	opioids, peripheral analgesics, regional analgesics, other
Postoperative delirium screening	on postoperative days 1–5 using 3DCAM, 4AT and CAM-ICU in the intensive care unit

The occurrence of postoperative delirium is assessed during daily rounds by trained staff in the first five days after the operation, in accordance with the European guideline. The 3DCAM test and 4AT are used for this purpose.

Additionally, the CAM-ICU (Confusion Assessment Method for the Intensive Care Unit) is routinely used by medical staff in the intensive care unit. All three instruments are validated and reliable screening methods for detecting delirium [14,15].

Withdrawal from the study happens may occur after the patient revokes consent, the planned operation is canceled, or if the study protocol is violated. All study participants are visited on all five postoperative days. To determine the incidence of delirium and other complications, such as cardiac and pulmonary, only patients who have spent at least one night on a surgical ward after surgery and who have undergone at least one postoperative screening will be included. Patients who do not complete these criteria are excluded from the statistical analysis. This methodological approach ensures a careful and representative analysis of postoperative events.

A recruitment period of approximately 16 months is planned to include 266 patients. A dropout rate of 10% of the recruited patients will be tolerated. If the dropout rate exceeds this threshold, further recruitment will be undertaken. The conduct of this study was guided by the recommendations of the STROBE checklist (Strengthening the Reporting of Observational Studies in Epidemiology) to ensure transparency and scientific rigor. All relevant points of the checklist were considered in the planning and conduct of the study to maximize the quality and reproducibility of the results.

